### Recruitment

Recruitment will be made from various high schools in Romania.

### Assignment to study group

The participants will be randomly assigned to one of the three trial arms (see Fig. 1). Randomization will be performed by a research assistant using a simple (unrestricted) randomization sequence that assigns one of three unique numbers (1, 2, or 3) per classroom enrolled in the intervention, signifying the experimental condition. No stratification will be employed. To conceal the allocation mechanism, the same research assistant will use sequentially numbered, opaque, sealed envelopes and will subsequently monitor the assessments and allow access to the application for the participants in the waitlist control group after 6 weeks. Two different research assistants will be responsible with enrolling the participants in the intervention and assigning them to the intervention by maintaining direct contact with student representatives from each classroom that is enrolled in the intervention. Neither the participants nor the psychologists involved in disseminating the intervention to the adolescents will be blinded, as blinding is not feasible given the context of the current trial. The principal investigator and the statisticians curating the dataset and running the data analysis will remain blinded to the study condition until the completion of the study.

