## Methods/design

### Trial design

This study is an exploratory randomized clinical trial involving comparisons at three time points (i.e., pre-intervention, post-intervention, 1 month follow-up) between three conditions: (a) automated intervention (consisting of an online, automated delivery of the intervention), (b) blended intervention (online automated delivery of the intervention plus regular contact with facilitators), (c) waitlist, with an allocation ratio of 1:1:1. The contrast between the automated and blended interventions is meant to highlight whether contact with facilitators while receiving psychoeducational materials might have an additive effect.

The design of this study complies with the Consolidated Standards of Reporting Trials (CONSORT) guidelines [22] and follows the Standard Protocol Items: Recommendations for Interventional Trials (SPIRIT) Statement 2013 [23] (see also Additional file 1: SPIRIT checklist and schedule of enrollment, interventions, and assessments).

The current trial is part of a larger project that aims to assess adolescent mental health in Romanian high schools.

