### Sample size

R version 4.2.2 for Windows (R Foundation for Statistical Computing, Vienna, Austria) was used for the sample size calculation in a linear mixed-effect model (sjstats package). The R statistical computing environment will also be used for future model fitting and evaluation.

We used appropriate methods for two-level-designs [25] to determine sample size requirements for a cRCT with 3 experimental groups, 4 classrooms per experimental condition, 22 participants per cluster. For our linear mixed-effects model, a sample size of approximately 88 participants per experimental condition for a total sample size of 264 was sufficient to achieve 80% power to detect an effect size of Cohen’s *d* = 0.4 at an alpha level of 0.05. A medium effect size was assumed based on previous work on digital mental health literacy interventions [26].

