#### Statistical methods

Our study will consist of a multisite cluster randomized trial in which the unit of measurement is at student-level, while randomization takes place at the unit of assignment, at classroom-level. Consequently, it is a low bias cluster-level RCT with potential joiners (i.e., individuals not in intervention clusters at random assignment but who enter later) being excluded and scant possibility of “contamination” or “treatment spillover” to the control classrooms. Analyses will employ linear mixed model with individual-level repeated measures nested within classrooms, nested within schools. Adhering to WWC group design standards [42], the model will include indicators for each intervention period and interaction terms for assignment to the intervention group and the period associated with the intervention. We will also report on robust standard errors from our fitted models to adequately account for dependence within clusters.

Nevertheless, youth research, and especially youth mental health research, has unique challenges concerning data gathering. First, although we adhere to a strategic research design to reduce missing data, patterns of attrition relating to individual and cluster-level factors will be investigated, including links to social and health variables. Second, challenges in gathering parental consent after classroom-level assignment to experimental condition would yield higher number of leavers, which constitutes individual-level attrition [42]. If data is missing at random, our analytic choice will yield unbiased estimates of treatment effects [43]. If data is missing not at random, weighting and multiple imputation would be used. In line with WWC standards [42] for cluster-level assignment RCTs, we will employ regression imputation, maximum likelihood, or nonresponse weights to address missing values while providing evidence that the approach appropriately adjusts the standard errors for clustering.

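### Simple randomisation of about 12 classrooms is unlikely to give the 4-per-arm layout behind the sample size, and risks a very small or empty arm

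*Protocol article*

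**What the plan says.** All points are from the protocol article.

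- **Trial design** describes three arms (automated, blended, waitlist) "with an allocation ratio of 1:1:1" and calls the trial exploratory.
- **Assignment to study group** specifies a "simple (unrestricted) randomization sequence that assigns one of three unique numbers (1, 2, or 3) per classroom enrolled in the intervention" and adds "No stratification will be employed".
- **Statistical methods** confirms that "randomization takes place at the unit of assignment, at classroom-level". The planned model has repeated measures on students within classrooms within schools, with assignment-by-period interactions.
- **Sample size** is worked out for "3 experimental groups, 4 classrooms per experimental condition, 22 participants per cluster", giving "approximately 88 participants per experimental condition for a total sample size of 264". This "was sufficient to achieve 80% power to detect an effect size of" d = 0.4 at alpha 0.05.
- **Study setting** and **Inclusion and exclusion criteria** draw classrooms from several state and private schools and from grades 9 to 12.

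No blocking, matching, minimisation or other restriction is described. The article positively states an unrestricted method and rules out stratification, so this is not a detail left to another document.

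**The concern.** Simple randomisation balances arm sizes well when hundreds of units are allocated. Here the units are classrooms, and the plan has about 12. Nothing in the procedure holds the arms at the four classrooms each on which the sample size was computed.

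Two things are at stake:

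- **Precision.** For a fixed number of classrooms, unequal arms usually widen at least some of the pairwise contrasts.
- **Feasibility in the tail.** If an arm has a single classroom, that arm's own data cannot separate its effect from the effect of that classroom. If an arm is empty, its comparisons are lost. If that arm is automated or blended, so is the third objective, the comparison of delivery formats.

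The spread of schools, school types and grades over arms is also left to chance. Mathematics and reading performance are among the primary outcomes and plausibly differ on these factors.

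**Working it through.** **Inputs.** Three arms, 4 classrooms per arm and 22 students per classroom (Sample size); an independent draw per classroom (Assignment to study group). The probability of 1/3 per arm is read from the 1:1:1 ratio (Trial design).

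**The plan's own figures.** 4 × 22 = 88 per arm and 3 × 88 = 264 in total, so the stated sizes need exactly 4 classrooms in every arm. The stated 80% power could not be reproduced, because the intraclass correlation (ICC), sidedness and repeated-measures correlation are not given. The probabilities below do not depend on it.

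**Distribution of arm sizes with 12 classrooms.** There are 3^12 = 531,441 equally likely sequences.

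- Exactly 4:4:4: 12!/(4!·4!·4!) = 34,650; 34,650/531,441 = 6.5%.
- At least one empty arm: 3·2^12 − 3 = 12,285; 12,285/531,441 = 2.3%.
- Over all splits, the smallest arm has 0, 1, 2, 3 or 4 classrooms with probability 2.3%, 13.8%, 35.7%, 41.7% and 6.5%.
- One or none in some arm: 2.3% + 13.8% = 16.1%.
- The most likely pattern is 3/4/5, at 31.3%.

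**Effect on a pairwise contrast.** With a and b classrooms in the two arms, the classroom-level variance is proportional to 1/a + 1/b. At 4 v 4 this is 0.5, so the ratio is (1/a + 1/b)/0.5. Examples: 3 v 5 gives (0.333 + 0.200)/0.5 = 1.07; 2 v 4 gives (0.500 + 0.250)/0.5 = 1.50. Over all splits with no empty arm, the mean ratio is 1.24 and the median 1.07. A minority of extreme splits pulls the mean up.

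**Illustrative power.** This assumes a two-sided pairwise test, the normal approximation, SD 1, and an ICC that the article does not give. The design effect is 1 + 21 × ICC. At 4 v 4 and ICC 0, power is Φ(0.4/√(2/88) − 1.96) = Φ(2.65 − 1.96) = 75.6%. The average under simple randomisation counts an empty arm as zero power.

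| Assumed ICC | Fixed 4 v 4 | Average, simple randomisation | Loss (points) |
|---|---|---|---|
| 0 | 75.6% | 67.7% | 7.9 |
| 0.01 | 67.4% | 60.1% | 7.3 |
| 0.05 | 45.7% | 40.6% | 5.1 |

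**If more classrooms enrol.**

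| Classrooms | Exactly equal split | Some arm with one or none |
|---|---|---|
| 12 | 6.5% | 16.1% |
| 15 | 5.3% | 5.8% |
| 18 | 4.4% | 2.0% |
| 24 | 3.4% | 0.2% |

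**Schools.** The number of schools and of classrooms per school is not given. For illustration, three classrooms from one school cover all three arms with probability 6/27 = 22.2% and all fall in one arm with probability 3/27 = 11.1%.

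**The case against.** The other side has real force. Simple randomisation is valid, unpredictable and openly declared, and the trial calls itself exploratory. An exactly equal split is improbable at any number of classrooms, so 6.5% says that the planned layout is unlikely but does not measure the damage. The median variance ratio of 1.07 shows that the typical loss is small. The 264 is described as sufficient, not as a cap, and the tail risk falls quickly if more than 12 classrooms enrol.

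A reader might also infer four stronger claims, none of which the article supports:

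- **That the allocation contradicts 1:1:1.** It does not. Equal probabilities meet that ratio in expectation; only the sample size needs 4:4:4.
- **That school and grade will be unbalanced.** They are left to chance, and the article gives nothing from which to size an imbalance.
- **That chance imbalance would dominate or bias the contrasts.** Outcomes are measured before the intervention and the model uses assignment-by-period terms. Stable level differences between schools, grades or classrooms therefore drop out, and only differences in change over time would matter.
- **That two classrooms in an arm already confound arm with classroom.** Complete confounding needs a single classroom. Two give poor precision, so the 51.8% chance of an arm with two or fewer is not the chance of that failure.

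What remains is the average loss of precision and, at the planned size, about a one-in-six chance of an arm with one classroom or none. Neither the exploratory label nor the mixed model makes up for such an arm.

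**Conclusion.** The point holds as a mismatch between the allocation method and the layout that the sample size assumes. The typical cost is modest. The tail is serious and avoidable: 16.1% for an arm with one classroom or none, including 2.3% for an empty arm. The consequence is lost precision and possibly a comparison that cannot be made, not bias.

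The probabilities are exact for 12 classrooms drawn independently with probability 1/3 each. They rest on 12 being the number actually randomised, which is the planning figure and not a stated limit. The power losses of about 5 to 8 points rest further on assumed ICCs and a simple pairwise test. This is a cheap improvement worth making while classrooms remain to be allocated.

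**What to change.** For all classrooms not yet assigned, replace simple randomisation with restricted randomisation that equalises the number of classrooms per arm. Two workable forms:

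- **Constrained allocation** to 4:4:4 (or as near as the allocations already made permit), balanced on school and grade. This suits the case where the remaining classrooms are known in advance.
- **Permuted blocks of three within school**, randomising all of a school's enrolled classrooms together. Where a school's classrooms do not come in threes, this alone does not guarantee equal totals.

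Include the blocking factors in the analysis model, and state the method in Assignment to study group.

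**Costs.** Recruitment has begun (Trial status), so allocations already made cannot be undone. The change needs a protocol amendment, notified to the ethics committee (Auditing) and updated on the registry (Ethics and dissemination). The last allocation in a block becomes more predictable; randomising a school's classrooms together limits this. Blocks within school also put all three arms in more schools: every full block does so, against 22.2% for three classrooms under the present method. Classrooms of one school can already fall in different arms, so this opens no new route for spillover but increases exposure to it.

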### Objectives

The goal of this study is to test the effectiveness of an intervention designed to promote mental health literacy in adolescents, in the format of a randomized clinical trial.

We aim to (1) determine whether this intervention has an impact on mental health, (2) observe if this intervention has an impact on fostering academic performance, particularly in disadvantaged students (i.e., academic resilience), and (3) examine what type of intervention delivery is more effective: automated versus blended format.

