### General description of the tested application

SCHOLARS is a web-based mental health literacy intervention containing six modules as follows: Module 1: The Stigma of Mental Illness; Module 2: Understanding Mental Health and Mental Illness; Module 3: Information on Specific Mental Illnesses; Module 4: Experiences of Mental Illness; Module 5: Seeking Help and Finding Support; Module 6: The Importance of Well-being. These modules will have both text and videos through which the users will progress. Both the automated and blended interventions are designed to last for three months, with two modules being delivered per month. Participants are encouraged to go through the materials at their own pace and have the option to revisit previous modules as needed. Participants can access the intervention from any location.

The intervention can be accessed through a LimeSurvey link and is compatible with various devices such as computers, tablets, and mobile phones. To ensure that the intervention will be properly delivered through this medium, we initially conducted a brief pilot test on a convenience sample consisting of university students. No issues were encountered during this phase.

Detailed information about the intervention is available on the project's website, which is linked on the initial page of the intervention. This resource allows participants to learn more about the study team responsible for the development of the intervention as well as the associated written and visual materials. Additionally, participants can ask any specific questions by emailing the research team; the email address is provided in the consent form.

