### Study conditions

#### Experimental—automated intervention

This intervention will last for 3 months, with two psychoeducational modules delivered per month. The participants will receive a total of 6 modules, which will include both text and video-delivered information, as well as quizzes and practical activities.

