**Fig. 1 Fig1:**
[figure not shown]
SPIRIT figure highlighting the proposed timeline of the intervention and assessments

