### Data collection, management, and analysis

#### Data collection methods

The primary outcome measures are related to academic performance, well-being, and symptomatology, which will be collected at three time points: pre-intervention, post-intervention, and 1 month follow-up. Academic performance (math and reading comprehension) will be assessed with a sample of items taken from TIMSS (mathematics) and from PIRLS (reading comprehension) [27].

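### Waitlist release after six weeks has no stated starting point; counted from allocation or start, controls would get the application before both post-baseline assessments

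*Protocol article*

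**What the plan says.** The only rule in the article's text for opening the application to the waitlist arm is in Assignment to study group. After describing randomization and sealed envelopes, it says that the same research assistant will go on to monitor the assessments and "allow access to the application for the participants in the waitlist control group after 6 weeks". It names no event from which the six weeks are counted.

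The other timings are these:

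- General description of the tested application: "Both the automated and blended interventions are designed to last for three months, with two modules being delivered per month". The same section adds: "Participants are encouraged to go through the materials at their own pace".
- Study conditions, automated arm: "This intervention will last for 3 months, with two psychoeducational modules delivered per month", six modules in total. The blended arm has the same duration and pace.
- Trial design: "comparisons at three time points (i.e., pre-intervention, post-intervention, 1 month follow-up) between three conditions".
- Data collection methods, on the primary outcomes: "which will be collected at three time points: pre-intervention, post-intervention, and 1 month follow-up".

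The waitlist is the only arm without the intervention. Under Statistical methods, the planned mixed model has period indicators and interactions between assigned group and period. Fig. 1 is captioned "SPIRIT figure highlighting the proposed timeline of the intervention and assessments", and Trial design refers to Additional file 1 for the schedule. Neither was available for this review.

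**The concern.** A waitlist arm serves as an untreated comparator only while its members are still waiting. Here the waiting time is six weeks, the intervention lasts three months, and the two post-baseline assessments come at its end and one month later. If the clock starts at allocation or at the start of the intervention, the waitlist classrooms receive the application about halfway through, before either assessment.

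The automated-versus-waitlist and blended-versus-waitlist contrasts would then compare immediate with delayed access, while the model would still label the waitlist classrooms as controls. If the intervention works and the waitlist students use it, both contrasts shrink. That affects Objective 1 ("determine whether this intervention has an impact on mental health") and Objective 2, on academic performance. A null result could mean either no effect or a control arm that had also received the intervention. Analysis could not recover an unexposed comparison, because no post-baseline assessment is planned before week 6. Objective 3, automated against blended, does not involve the waitlist arm and is unaffected.

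**Working it through.** The six weeks is a design choice, so there is no formula to reproduce it. The check is calendar arithmetic.

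**Inputs from the article:** release after 6 weeks; intervention of 3 months; follow-up 1 month later; 2 modules per month, 6 in total.

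**Assumption:** a month is between 4 weeks and 365.25/12/7 = 4.348 weeks. Post-intervention is taken at 3 months from start and follow-up at 4 months.

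**Assessment weeks, counted from start**

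- Post-intervention: 3 × 4 = 12 to 3 × 4.348 = 13.0.
- Follow-up: 4 × 4 = 16 to 4 × 4.348 = 17.4.

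**Release week and prior access, by starting point of the six weeks**

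| Six weeks counted from | Release week | Access before post-intervention | Access before follow-up |
|---|---|---|---|
| Start | 6 | 12 − 6 = 6 to 13.0 − 6 = 7.0 weeks | 16 − 6 = 10 to 17.4 − 6 = 11.4 weeks |
| End of intervention | 12 + 6 = 18 to 13.0 + 6 = 19.0 | 0 | 0 |
| Follow-up | 16 + 6 = 22 to 17.4 + 6 = 23.4 | 0 | 0 |

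If allocation comes some time before the start, counting from allocation puts release earlier still, so the first row is a lower bound for that case. In the second row, release comes 18 − 16 = 2.0 to 19.0 − 17.4 ≈ 1.7 weeks after follow-up.

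**Content available to controls under release at week 6**

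Modules available = 2 × (weeks of access) / (weeks per month).

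- By post-intervention: 2 × 6/4 = 3.0 to 2 × 7.04/4.348 = 3.2 of 6.
- By follow-up: 2 × 10/4 = 5.0 to 2 × 11.39/4.348 = 5.2 of 6.

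If all modules opened at once on release, which is an assumption and not the stated pace, all 6 could be available at both assessments. The range is therefore 3 to 6 modules at post-intervention and 5 to 6 at follow-up. This is content made available, not content used. No loss of power is derived from it, because that would need an assumed link between access and effect that the article does not give.

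**The case against.** The strongest reply is that the stated figures can all hold together. Six weeks from the end of the intervention puts release about two weeks after follow-up and keeps the control arm unexposed at every assessment. That suits the purpose of a waitlist, and of the three starting points tabulated it is one of two that give no exposure. The sentence also mentions monitoring the assessments before it mentions release, which is compatible with a later starting point. The timeline figure and the supplementary schedule are natural places for the release point, and an item that cannot be seen there cannot be called missing from the plan. Finally, any bias would need early release, uptake by waitlist students and a real effect, and the Discussion itself expects that adherence may be limited.

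Most of this stands. A reader might infer that the protocol contradicts itself, or that the control arm will be contaminated. The documents support neither inference, because a coherent reading exists and nothing shows that early release took place.

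What remains is that the sentence gives an operating number in a paragraph about allocation, where the end of the intervention is not mentioned. A research assistant following it literally could open the application at week 6. The remark under Statistical methods that contamination of control classrooms is unlikely does not settle this. It sits beside the exclusion of late joiners and speaks of spillover, gives no release date, and supports the later reading only weakly.

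**Conclusion.** The point holds as an ambiguous operating rule with one harmful reading. It is worth correcting, with medium confidence.

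If the six weeks run from allocation or start, neither waitlist contrast has an unexposed control at any post-baseline assessment, and the estimates for Objectives 1 and 2 would tend towards no difference. That direction depends on the intervention having an effect and on waitlist students using it. If the six weeks run from the end of the intervention or from follow-up, exposure before both assessments is zero and the design is sound on this point.

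The text does not choose between these readings. Fig. 1 or Additional file 1 may do so. If they show a later release, only the wording of the sentence is at fault; if they show week 6, the harmful reading is confirmed.

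**What to change.** In Assignment to study group, replace the six-week rule with an event-based one: *The application is released to each waitlist classroom only after that classroom's 1-month follow-up assessment has been completed.* Make the timeline figure agree. This rule keeps the control arm unexposed whichever starting point was intended.

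Recruitment had begun when the article was written (Trial status), so check whether any waitlist classroom has already been given access. Only if one was released before an assessment, record its release date, report the affected contrast as immediate versus delayed access, and do not read a null result there as absence of effect.

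The cost is one sentence, a matching figure and control over when the link opens. Under the article's own rules, a protocol change also goes to the ethics committee (Auditing) and to the ClinicalTrials.gov record (Ethics and dissemination). No extra participants or assessments are needed. Waitlist students would wait about 10 to 11 weeks longer than under release at week 6 (16 − 6 to 17 − 6). They would wait no longer than under a count from the end of the intervention (week 18 to 19), provided follow-up is completed on schedule.
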